### Sample size considerations

Planned enrollment of 500 ALI cases guarantee an adequate sample size for LIPS validation. If we have 500 ALI cases and 80% score above the threshold for the ALI model (sensitivity) then our precision will be .02 and the 95% CI would 0.78 to 0.82.

A comparison of 500 ALI cases with 500 propensity matched high risk controls will allow us to determine moderately high associations (odds ratio >2.0) between common in-hospital exposures (prevalence >5%, i.e. variability in fluid management, transfusion, antibiotics, FIO2, mechanical ventilation) and ALI development (Figure 3). We will be able to identify only strong associations for less common in-hospital exposures (<5%).

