### Statistical Analysis

An estimate for the probability of ALI development will be calculated for each patient based on the LIPS model. Because of subjective nature of clinical definitions used to identify the outcome of our study, it is necessary to assess interobserver variability. Interobserver agreement for ALI development will be assessed by calculating the Kappa statistic, using a threshold of 0.6 as an indication of acceptable interobserver agreement.

The calibration and discrimination of model will be assessed using the Hosmer-Lemeshow goodness-of-fit test and the receiver operating characteristic curve, respectively. An area under the ROC curve greater than 80% will be considered to be the evidence of good model discrimination. Using a LIPS cutpoint of 3.5 or more identified in the preliminary data, the comparison of the model prediction versus the actual event observed will be summarized by a simple 2 by 2 table reporting ALI propensity versus ALI development. Summary measures, based on the 2 by 2 table, will be reported: sensitivity, specificity, positive predictive value, negative predictive value, positive and negative likelihood ratios along with their 95% confidence intervals.

In a matched case-control design the associations suggested by preliminary clinical studies (Table 3) will be compared between ALI cases and high risk controls propensity matched by age, gender and the probability of ALI development at the time of hospital admission (LIPS, see above). Subpopulation analyses will be performed to determine what hospital exposures are associated with ALI in low/moderate ALI risk patients and what hospital exposures factors are associated with no ALI development in high ALI risk patients. The primary statistical endpoint is the development of ALI at any time during hospital stay. The matching is based on ALI risk at admission and the exposure period at risk. For example, if a hospitalized patient, who has an estimated propensity for developing ALI of 20% actually develops ALI 10 hours after hospital admission the exposures in matched control patient is only measured during the initial 10 hours after hospital admission. Paired statistics will be used for group comparisons. A conditional logistic regression model will be built in the case of baseline imbalances.

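### The 95% confidence interval given for LIPS sensitivity (0.78 to 0.82) is about plus or minus one standard error; 500 ALI cases give about 0.765 to 0.835

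*Protocol article*

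**What the plan says.** The Sample size considerations section of the protocol article opens with a claim about validation: "Planned enrollment of 500 ALI cases guarantee an adequate sample size for LIPS validation". The support follows at once. The condition is "If we have 500 ALI cases and 80% score above the threshold for the ALI model (sensitivity"), and the consequence is "then our precision will be .02 and the 95% CI would 0.78 to 0.82".

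The Statistical Analysis section says how the sensitivity will be obtained. The score is dichotomised ("Using a LIPS cutpoint of 3.5 or more identified in the preliminary data") and cross-tabulated against observed ALI. Sensitivity, specificity, the predictive values and the "positive and negative likelihood ratios along with their 95% confidence intervals" are then reported. The confidence level is thus 95% in both places. No other denominator, confidence level or adjustment is given for the sensitivity.

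**The concern.** All the inputs to a single-proportion confidence interval are in the one sentence (500 cases, 0.80, 95%), and the interval printed beside them looks too narrow. A half-width of 0.02 is close to the standard error itself, which suggests that the normal multiplier was not applied.

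At stake is the stated precision for the validation aim. No other figure in the article supports 500 cases for that aim: the remaining calculations concern exposures, survival and quality of life. Validation is not a side issue, since the LIPS probability is also a matching variable for the case-control comparison, and defining the high-risk population is the first deliverable listed in the Conclusion. A reader who takes the printed interval at face value would expect the proportion of ALI cases missed at the cutpoint to be known to within 18% to 22%. The design gives about 16.5% to 23.5%.

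**Working it through.** **Inputs**

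- n = 500 ALI cases (Sample size considerations).
- p = 0.80, so 400 of 500 cases at or above the cutpoint (same sentence).
- Confidence level 95%, z = 1.96 (same sentence, and Statistical Analysis).

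**Step 1: reproduce the printed figure**

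SE = sqrt(p(1 − p)/n) = sqrt(0.8 × 0.2 / 500) = 0.0179, which rounds to 0.02.

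p ± 1 SE = 0.80 ± 0.0179 = 0.782 to 0.818, which rounds to 0.78 to 0.82.

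With 500 cases, the printed precision and both limits are therefore recovered with a multiplier of 1 instead of 1.96.

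**Step 2: the 95% interval from the same inputs**

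| Method | Formula | Result |
|---|---|---|
| Wald | p ± z·SE = 0.80 ± 1.96 × 0.0179 | 0.765 to 0.835 (half-width 0.0351) |
| Wald with continuity correction | half-width z·SE + 1/(2n) = 0.0351 + 0.001 | half-width 0.0361 |
| Wilson | [p + z²/2n ± z·sqrt(p(1 − p)/n + z²/4n²)] / (1 + z²/n) | 0.763 to 0.833 (half-width 0.0350) |
| Clopper-Pearson | beta quantiles for 400/500 | 0.762 to 0.834 |

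None of these gives a half-width of 0.02. A one-sided 95% multiplier does not either: 1.645 × 0.0179 = 0.029.

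**Step 3: could rounding or another denominator explain it?**

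- *Rounding.* For a 95% half-width to round to 0.02 it must be below 0.025. At p = 0.80 this needs n > 1.96² × 0.16 / 0.025² ≈ 983. Rounding cannot explain the figure at n = 500.
- *All 1,000 case-control patients.* Half-width = 1.96 × sqrt(0.16 / 1000) = 0.0248, limits 0.775 to 0.825, which also round to the printed values. But the denominator of sensitivity is the ALI cases alone, and the sentence names 500 of them.
- *A different sensitivity.* With 500 cases, a half-width of 0.02 would require a sensitivity of about 0.945, not the stated 0.80.

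**Step 4: size of the error**

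- Ratio of true to stated half-width: 0.0351 / 0.02 = 1.75. Against the unrounded standard error the ratio is 1.96; the two differ only because 0.0179 was rounded up to 0.02.
- Coverage of ±0.02: 2Φ(0.02 / 0.0179) − 1 ≈ 0.74. For the unrounded ±1 SE it is about 0.68.
- Cases for a true ±0.02 at p = 0.80: 1.96² × 0.16 / 0.02² ≈ 1,537, about 3.1 times the 500 planned. This only gauges the error; the article does not require ±0.02.

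**The case against.** The arithmetic is hard to defend, so the best case on the other side concerns weight and wording.

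- **Little depends on the interval.** It is a conditional illustration. No sample size is solved from it and no decision rule uses it. The numerical criterion for discrimination is an area under the ROC curve above 80%. The reported intervals will be computed from the observed data, so no estimate or test changes. *This stands*, and it limits the consequence to the planning statement.
- **The number 500 has other support.** The Abstract and the rest of the sample size section base 500 cases and 500 controls on power for exposures and outcomes. *This stands for those aims.* It does not help the validation aim, for which this interval is the only figure.
- **The text guarantees an adequate sample size, not a given precision.** *True as a reading of the words.* But the precision is the sole evidence offered for adequacy, so the guarantee has no correct figure behind it.
- **The cause is inferred.** No working is shown, so the missing multiplier is a likely explanation and not a fact; use of 1,000 patients as the denominator would print the same rounded limits. *This stands, but changes nothing:* the interval is wrong for 500 cases whatever its origin.

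**Conclusion.** The concern holds. With 500 ALI cases and sensitivity 0.80, the 95% half-width is 0.035, not 0.02, and the interval is about 0.76 to 0.83 or 0.84 depending on the method. The stated half-width is too small by a factor of about 1.75, and the error flatters the design.

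This rests only on the article's own three inputs and on treating the cases as independent with a common probability of scoring above the cutpoint. Every standard 95% method tried leads to the same conclusion.

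The finding is limited to the stated precision. It does not imply that 500 cases are inadequate: ±0.035 may well be acceptable, and the article sets no threshold against which to judge it. The power statements for exposures, survival and quality of life are unaffected.

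**What to change.** Replace the precision sentence with, for example: *With 500 ALI cases and a sensitivity of 0.80, the standard error is 0.018 and the 95% confidence interval (Wilson) is about 0.76 to 0.83, a half-width of 0.035.* If the Wald interval is preferred, give 0.765 to 0.835. Name the method either way, so that the limits and the half-width can be checked against each other.

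Then either remove the word claiming a guarantee from the opening sentence, or say why a half-width of 0.035 is sufficient for the intended use of the 3.5 cutpoint.

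The cost is one or two sentences and a less favourable stated precision. No extra patients and no change to the design or analysis are needed.

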**Figure 3 F3:**
[figure not shown]
**Power for a matched case control study of 500 ALI patients matched to 500 controls where the risk factor occurs at 10%, 5%, or 1% prevalence in the controls and the false positive rate is 0.05**. As depicted, if 5% of the controls experience delayed fluid resuscitation which increases the risk of ALI by 2 fold, then the study has about 82% power to reject the null hypothesis.

Assuming a median survival of around 2 years in control population and ALI increases the risk of death by about 1.25, then the study has 80% power to reject the null hypothesis of equal survival of controls and ALI patients. A target of 100 ALI survivors and 100 controls assuming a standard deviation of the health related quality of life score among ICU patients of 10 units, the study has 80% power to detect a difference in self reported quality of life of 4.0 units or greater.

## Discussion

The LIPS study is a population based observational cohort study that aims to identify patients at high risk of developing ALI early in the course of illness (at the time of hospital admission), and compare the in-hospital (second hit) exposures and outcomes of patients at high risk who do and do not develop ALI. Analysis and comparison of exposures and outcomes between patients at high risk identified before ALI development is essential to understand clinical pathogenesis of ALI and design effective prevention strategies. By determining not only candidate interventions, but also the attributable burden of ALI, it will allow the prioritization of preventive strategies and future clinical trials.

Olmsted County offers a unique opportunity to study potential ALI prevention targets in a geographically defined population because all the critically ill patients from the county are admitted to Mayo Clinic hospitals. The use of population based sample eliminates the referral bias common in clinical studies performed at tertiary care institutions[23]. As a part of study design we have developed a near real time access to pertinent data in electronic medical records to identify patients from the community with or at high risk of ALI. The electronic infrastructure will greatly facilitate to conduct this population based study by minimizing study coordinator time necessary to screen large number of patients. Time-sensitive biospecimen collection in a population of patients with strictly defined phenotype and detailed capture of environmental exposures will allow for the development of important biospecimen repository for future collaborations in Genome Wide Association and plasma biomarker studies.

The principal limitation of our study is imposed by the broad nature and definition of the primary outcome of interest, ALI [21]. The exclusion of left atrial hypertension poses a particular challenge in the clinical assessment of ALI. In addition to using a standardized definition and extensive training of study personnel, all ALI cases will be reviewed by trained expert investigators. There is a possibility of ascertainment bias as we will depend on the clinicians caring for the patient to order the chest x-ray and the arterial blood gas necessary to diagnose ALI. Fortunately, almost all patients requiring respiratory support do have these tests performed routinely every day. It is therefore extremely unlikely that a significant ALI would occur without the need to perform the chest x-ray and the arterial blood gas as a part of clinical care.

Additional limitations of our approach come from the observational design of this study. First, because participants are not randomly assigned to the exposures under investigation, our study is particularly prone to indication bias, in that patients receiving certain therapies may be systematically different from those not receiving the therapies. If these differences are associated with the outcome of interest, the study results may be biased. Large sample size and a comprehensive collection of exposure variables will mitigate the potential bias by enabling our statisticians to adjust for any measured factor found to predict the use of each exposure under investigation. However, some important factors may be unknown or unmeasured, resulting in residual confounding and bias. The population based sample is clearly a strong point of our study. However, all patients will be treated in the two hospitals of the single teaching medical center, and, although internal validity will be high, the study results may not generalize to patients in other settings. Moreover, we will not be able to take advantage of additional variability in practice such as would be possible in multicenter studies involving different parts of the world. Long study period raises another question about whether the exposures, prognosis, and incidence of ALI will be stable enough to allow the proposed investigation. Fast pace changes in health care delivery and quality improvement initiatives could plausibly lead to the change in frequency of some of the proposed in-hospital exposures. Should changes in practice occur during the study period, our detailed observation of both practice and outcomes will give us an opportunity to correlate changes in practice with the development and outcome of ALI and possibly be able to make stronger causal inferences from the observed associations.

This causal translational research study will not affect the outcome of studied patients (this is a non-intervention epidemiologic study) but will help in better understanding the clinical pathogenesis of ALI and the design of future ALI prevention strategies. Since the therapeutic options are limited once ALI develops, the prevention is paramount. Unfortunately, effective prevention interventions do not currently exist, and our knowledge about clinical pathogenesis of ALI is limited. By identifying patients at high risk earlier (in the emergency department and operating room), and collecting biospecimens and clinical data before ICU admission we hope to improve our understanding of ALI and identify targets for future quality improvement interventions and ALI prevention trials. Previous studies have concentrated on patients in the ICU with already established ALI. Hence the inferences from these studies with regards to ALI pathogenesis and potential prevention targets are limited.

Potential future prevention strategies include, but are not limited to 1) quality improvement interventions to limit specific hospital acquired exposures (delayed treatment of infection and shock, aspiration triggers, high tidal volume ventilation, plasma transfusion from alloimmunized donors), and 2) the use of systemic and inhaled anticoagulants, antiplatelet agents, anti-inflammatory drugs and antioxidants. Some of these therapies have already been tested in preliminary clinical trials with encouraging result. This is in contrast to uniformly negative results of mechanistic interventions when applied later in the course of illness, once ALI is established.

## Conclusion

This population based observational cohort study will define 1) the population of patients at high risk for ALI at the time of hospital admission 2) the most significant second hit in-hospital exposures that may modify the development and progression of ALI and 3) attributable burden of ALI in the community. The results will inform future mechanistic studies and clinical trials with an ultimate goal of preventing this devastating complication of critical illness.
